### Diagnostic Accuracy

The measure of diagnostic accuracy for the main objective will be the accuracy of PCR for the detection of *M leprae*. We will also calculate specificity and sensitivity of the method and of real-time PCR for the detection of *M leprae* viability. AUC will be calculated for quantitative variables obtained using ultrasound examination.

### Ethical Considerations

All patients willing to participate in this study will be required to sign an informed consent form before data collection begins. This study has been approved by the University of Brasília’s Research Ethics Committee under the number 85116624.2.0000.5558 on March 29, 2025, and adheres to the Declaration of Helsinki regarding ethical principles for human subject research. Patients will not be financially compensated.

### Study Registration

The study was registered on Plataforma Brasil [35]. It is also registered on ClinicalTrials.gov under the number NCT07515989.

### Data Collection

To safeguard sensitive information, study data will be collected and managed using the REDCap (Research Electronic Data Capture; Vanderbilt University) tool hosted at the University of Brasília. REDCap is a secure, web-based software platform designed to support data capture for research studies, providing (1) an intuitive interface for validated data entry, (2) audit trails for tracking data manipulation and export procedures, (3) automated export procedures for seamless data downloads to common statistical packages, and (4) procedures for data integration and interoperability [36,37].

## Results

Grant funding for this study was received in May 2023, August 2023, and June 2026. As of October 2025, no patients have been enrolled in this study. Participant recruitment started in January 2026 and is scheduled to end in December 2026. We expect to recruit 108 patients with suspicion of leprosy consecutively in this time frame, of whom half are expected to have the disease and half are expected to have other diagnoses, serving as nonleprosy controls. Collection of clinical and laboratorial data will follow the same schedule as that of recruitment. Data analyses are expected to begin in February 2027 and end in July 2027, with findings expected to be submitted for publication by August 2027.

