**Methods:**

This will be a diagnostic study with consecutive prospective recruitment of patients referred to the leprosy outpatient clinic of University Hospital of Brasília for diagnosis and treatment. During follow-up, clinical and molecular examinations will be performed, and their results will be compared to the sonographic findings, which will be collected monthly for 1 year. Patients will be evaluated clinically, via ultrasound, and molecularly in 2 stages of leprosy diagnosis and treatment: immediately after clinical diagnosis and 1 year after the start of treatment. Subcutaneous aspiration of the ulnar nerve will be performed in the ulnar tunnel guided by ultrasound. The aspirated material will be used for identification of bacillary DNA and RNA at the time of diagnosis and 1 year after the start of treatment.

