## Methods

### Study Design and Population Studied

This is a diagnostic study with prospective collection. Patients aged 14 years or older will be enrolled after agreeing to and signing the informed consent form. The informed consent form will be signed by the responsible adult in the case of participants under 18 years of age. This research is in line with the Declaration of Helsinki and its revision made in 2013.

The case definition will be determined by a professional external to the investigation according to the standard procedures of the leprosy outpatient clinic of the UHB, which consist of clinical history, general physical examination, and dermato-neurological examination. Case definition will follow the World Health Organization (WHO) composite reference standard for the diagnosis of leprosy [32]. Direct investigation of the bacillus will be performed via SSSs of lesions, earlobes, and elbows. After the procedure, collected material from perineural aspiration and dermal lesions will be sent to the laboratory within a maximum period of 24 hours. The results of the perineural aspiration will only be known to researchers by the end of the study. Morphological data described in the ultrasound examination will be accessed by a blinded ultrasound specialist based on deidentified ultrasound images.

Clinical and molecular examinations will be performed, and their results will be compared to the sonographic findings, which will be collected monthly for 1 year. Molecular findings will be compared to the composite reference standard. Patients will be evaluated clinically, via ultrasound, and molecularly immediately after clinical diagnosis and 1 year after the start of treatment.

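### Data collection is dated to end with recruitment in December 2026, before any leprosy patient can reach the 1-year evaluation that the protocol requires

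*Protocol article*

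**What the plan says.** The calendar is given in the Results section, and the Abstract (Results) gives the same dates and the same statement on data collection.

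- Recruitment: "Participant recruitment started in January 2026 and is scheduled to end in December 2026".
- Data collection: "Collection of clinical and laboratorial data will follow the same schedule as that of recruitment".
- Analysis and reporting: "Data analyses are expected to begin in February 2027 and end in July 2027", "with findings expected to be submitted for publication by August 2027".

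The follow-up is set out in Methods, Study Design and Population Studied: "Patients will be evaluated clinically, via ultrasound, and molecularly immediately after clinical diagnosis and 1 year after the start of treatment". That section also has ultrasound findings gathered every month over a year. The Abstract (Methods) adds that the aspirate serves for "identification of bacillary DNA and RNA at the time of diagnosis and 1 year after the start of treatment".

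Rationale for the Study makes clinical, molecular and ultrasonographic follow-up the general objective, and its first specific objective includes prognostic accuracy. The Abstract (Conclusions) looks ahead to bacillary viability before and after treatment. No section gives a later end of collection, a second data cut or a separate report for the 1-year data.

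On access to the PCR results, Study Design and Population Studied says: "The results of the perineural aspiration will only be known to researchers by the end of the study".

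**The concern.** A study that enrols over 12 months and follows each patient for 12 months must collect data for about 24 months. The article allows 12. Both sides of the conflict are stated outright, and the calendar is stated twice, so this is not detail that a condensed article has left out.

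At stake are the before-and-after RNA comparison, the clinical and ultrasound follow-up, and anything prognostic. If the dates were followed literally, these aims would have no 1-year data. If collection simply ran on without a new plan, any 1-year result in a 2027 analysis would rest on a subset of patients defined by early enrolment.

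**Working it through.** **Inputs**
- Recruitment and data collection: January to December 2026 (Results).
- Analysis: February to July 2027; submission by August 2027 (Results).
- Follow-up: 1 year from the start of treatment (Study Design and Population Studied; Abstract, Methods).
- Expected sample: 108 patients, half with leprosy, so 108 / 2 = 54 (Results; Sample Calculation).

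**Assumptions (not in the article)**
- Accrual is even from 1 January to 31 December 2026.
- Treatment starts at enrolment. It should not start materially earlier, because the first evaluation comes immediately after diagnosis. A later start pushes every date back.

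**Denominator.** The 1-year evaluation is timed from the start of treatment. Nonleprosy controls have no such date, so the counts use the 54 expected leprosy patients.

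**Step 1: length of collection.** The stated window is 12 months. The required window is accrual plus follow-up = 12 + 12 = 24 months, that is, January 2026 to December 2027.

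**Step 2: earliest and latest 1-year dates.** A patient enrolled on 1 January 2026 reaches 1 year on 1 January 2027. On 31 December 2026 that patient has 364 days of follow-up, and the average patient has about 6.0 months. A patient enrolled in December 2026 reaches 1 year in December 2027, about 4 months after the planned submission.

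**Step 3: leprosy patients at 1 year on each stated date.** Number = 54 × (days of 2026 recruitment whose 1-year anniversary has passed) / 365.

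| Date | Recruitment days at 1 year | Share | Of 54 |
|---|---|---|---|
| 31 Dec 2026, end of collection | 0 | 0% | 0 |
| 1 Feb 2027, earliest start of analysis | 32 | 8.8% | 4.7 |
| 28 Feb 2027, latest start of analysis | 59 | 16.2% | 8.7 |
| 31 Jul 2027, end of analysis | 212 | 58.1% | 31.4 |
| 31 Aug 2027, submission | 243 | 66.6% | 36.0 |

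Counting by whole months gives nearly the same result: 54 / 12 = 4.5 per month, so 4.5 after one month and 7 × 4.5 = 31.5 by the end of July 2027.

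**Step 4: what does not depend on follow-up.** The main finding is PCR accuracy at the preset Ct threshold (PCR Positivity Criteria; Diagnostic Accuracy) against the composite standard. Case Definition has that standard completed before the index test, and clinical data, ultrasound and aspirate collected on the same day. All of this exists by the end of December 2026, so a February 2027 start is feasible for it.

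**The case against.** The best defence is that the dates describe the baseline accuracy paper and that the sentence on data collection is merely too broad. That may be what was meant. The Abstract states accuracy of the aspirate as the aim and presents follow-up as an addition, and the February to July 2027 analysis suits baseline data. Two parts of this stand: the main accuracy result is untouched, and the remedy is a correction of dates and scope. But no section limits the calendar to baseline, and Rationale for the Study names follow-up as the general objective. As written, the sentence remains incompatible with the visits. Figure 1 is said to summarise the timeline, and its image is not in the text reviewed. It may show the later visits, but it would not change the dates in the text.

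Two stronger readings are tempting.

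- *The 1-year aims will be analysed on early recruits only, or on nobody.* The article does not say that 1-year data enter the 2027 analysis. It says only when analyses and submission are expected. This is a risk of the calendar and not a stated plan.
- *A February 2027 analysis will unblind the follow-up examinations.* The article says that aspirate results reach researchers only by the end of the study. It does not say that follow-up examiners would be given them. The nerve measurements come from deidentified images read by a third radiologist, and the reference standard is fixed at inclusion. Unblinding is possible but not documented.

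**Conclusion.** The point holds as an internal contradiction about the follow-up data. Under the stated collection window, 0 of the 54 expected leprosy patients can have a 1-year evaluation. That zero follows from the dates once treatment starts no earlier than enrolment, and it does not depend on the pattern of accrual. If collection ran on unannounced, about 5 of 54 would have reached 1 year by 1 February 2027 and about 31 to 32 of 54 by the end of July 2027. These two figures do rest on even accrual and on treatment starting at enrolment. Slower early accrual or later treatment starts would lower them. On no reading of the calendar are the 1-year data complete before December 2027.

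A reader might infer that the study's main result is in doubt. The documents do not support that, because the PCR accuracy comparison uses baseline data only.

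**What to change.** 1. In the Results section and the Abstract (Results), replace the sentence on data collection so that baseline collection follows recruitment and follow-up collection runs to the last 1-year visit, in December 2027 or later.
2. Limit the February to July 2027 analysis and the August 2027 submission to baseline diagnostic accuracy.
3. Add a second lock after the last 1-year visit, about January 2028, for RNA viability and for clinical and ultrasound follow-up. State that no 1-year conclusion will be drawn from the 2027 analysis.
4. As a precaution, state that follow-up examiners and the image reader stay unaware of individual PCR results until the second lock, and reword the sentence on access to aspirate results to match. Settle this before February 2027, since disclosure cannot be undone.

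Cost: an amendment of dates and wording, with no added patients or procedures. The start of the 1-year analysis moves from February 2027 to about January 2028, which is 11 months. With the same six-month analysis period, the 1-year report follows about 11 to 12 months after August 2027. The baseline paper keeps its date.

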## Discussion

### Expected Findings

The findings of this study are expected to support perineural aspiration as a viable diagnostic strategy for leprosy, particularly in early-stage, paucibacillary, and pure neural presentations. The application of PCR to perineural specimens will be demonstrated to have notable sensitivity and specificity in detecting *M leprae*, addressing inherent shortcomings of conventional diagnostic approaches that rely predominantly on clinical criteria and cutaneous sampling. This probable finding may transform the current management of a suspected leprosy case. Worldwide, leprosy diagnosis is based on the presence of at least one of three cardinal signs: (1) definite loss of sensation in a pale (hypopigmented) or reddish skin patch, (2) thickened or enlarged peripheral nerve with loss of sensation and/or weakness of the muscles supplied by that nerve, or (3) presence of acid-fast bacilli in an SSS [32]. Clinical examinations have limited sensitivity in multi-bacillary cases [38] and are not reliable when performed by inexperienced individuals [39,40]. These can be important factors for the re-emergence of the disease in low-prevalence areas where trained personnel and SSSs may not be widely available. SSS cytology has limited sensitivity, especially in early-stage, paucibacillary, and pure neural leprosy [32,41], being negative in approximately 70% of all cases [42]. PCR is the most accurate technique to detect *M leprae* in biological samples [13] and has been incorporated into reference laboratories of national health services in leprosy-endemic countries [43,44], with possible future application in primary care settings [14]. Thus, by ascertaining that PCR of the perineural aspirate is an accurate method to diagnose leprosy, we may be able to prevent disability by confirming early-stage, paucibacillary, and pure neural cases.

Through our study, we will be able to demonstrate a high sensitivity of the perineural aspirate in patients with paucibacillary forms of the disease. Preliminary studies in patients that have undergone nerve biopsies have shown both a high sensitivity (92% using PCR) [45] and higher bacillary index of nerve sampling compared to skin sampling [46]. The current diagnostic strategy, which samples for the microbiological diagnosis of leprosy from skin lesions, earlobes, and 3 to 6 representative skin locations [47,48], has an especially low sensitivity in paucibacillary, pure neural, and early-stage lesions [49,50], resulting in diagnostic delays, misdiagnosis [51], and mistreatment. Our potentially higher diagnostic sensitivity in paucibacillary forms is a consequence of the traditional pattern of sample collection not matching the pattern of distribution and homing of *M leprae* in the natural history of the disease. The peripheral nervous system seems to be the first to harbor this mycobacterium [52] and is the location of persistent parasites after treatment of multi-bacillary disease [53].

In this study, we will evaluate both RLEP and RNA targets (sodA and 16S). Previous studies have evaluated a variety of PCR targets to detect *M leprae* in tissues, with the most frequently used being RLEP [13]. Despite its high specificity, the use of this target can only detect 75% of patients with leprosy [13], and its positivity is not related to the viability of the microorganism [15]. We expect to obtain high assay sensitivity using these tests in parallel, as it has been proposed in other studies [14]. As *M leprae* viability is an important clinical question in leprosy, especially in terms of differentiating reaction from relapse, we will also use RNA targets. Their use better correlates with active microorganisms as this nucleic acid is less resistant to temperature and has a shorter half-life [54], being already used for viability evaluation in preliminary studies [15,41]. Thus, our proposed test is also expected to deliver information on the viability of *M leprae* in the aspirate.

The sample collection method is expected to be feasible in most primary care facilities. One of the main limitations of nerve sampling in the diagnosis of suspected leprosy has been the invasiveness of conducting nerve biopsies [55], which generally require sedation and anesthesia monitoring. However, less invasive nerve aspiration studies have been performed, being generally limited to clinically enlarged nerves [56,57]. The feasibility of the collection method proposed in our study will not be unexpected as ultrasound-guided aspiration has been used in other studies for previously inaccessible organs [58]. The use of ultrasound guidance will likely reduce the false negative rate compared to the conventional method. This will be in accordance with other studies using different samples, which have shown that guidance enhances the quality of the material obtained and improves diagnostic accuracy [20,59]. Tissue sampling via aspiration has already been shown to be feasible to collect interstitial fluids from many tissues, including orbits, eyelids, genitals, lymph nodes, and thyroid glands [58]. Similar to what we expect from our study, complications with the use of thin needles (less than 21G) are rare [58,60,61]. Using ultrasound guidance, we expect to arrive at a safe, minimally invasive collection method with high diagnostic yield suitable to be used in primary care facilities.

Although not planned in this study, the validation of this protocol may allow for the future use of the validated collection method to perform other targeted studies. In the realm of molecular evaluation, this methodology could be used to leverage specialized biomolecular markers, including circulating micro-RNAs and DNA methylation profiles, which are crucial for identifying early-stage pathologies [11,15]. The advancement of next-generation sequencing technologies and amplification techniques such as digital PCR could allow for the detailed capture of genetic and epigenetic information, providing a deeper understanding of molecular characteristics related to clinical prognosis and drug resistance [62].

One of the main limitations of this study is that aspiration will be performed in only 1 nerve. It is possible that aspiration of multiple nerves would increase the sensitivity of the method. On the other hand, this would greatly increase the time and resources needed to perform the procedure, affecting not only the feasibility of the study but also the applicability of the method in low-resource settings. Thus, collection in multiple nerves may defeat the purpose of being suitable to most primary care facilities. Additionally, the ulnar nerve is the most frequently involved in leprosy [63], and its assessment in the cubital tunnel is practical due to its proximity to clear anatomical landmarks [64].

### Conclusions

The integration of the procedures proposed in this protocol reinforces their clinical utility, emphasizing diagnostic precision and the reduction in invasive interventions. The implementation of similar methodologies has been demonstrated to result in significant reduction in the time between sample collection and definitive molecular diagnosis, as well as a decrease in operational costs compared to conventional protocols [26,28]. The proposed approach is expected to represent an important step toward personalized medicine, enhancing the capacity for early medical intervention and balancing technological innovation with cost-effectiveness and patient well-being [5].

## Data Availability

Deidentified data supporting the findings of this study will be available in the Dryad digital repository [65] following publication of the article.

## Abbreviations

AUC: area under the curve
cDNA: complementary DNA
CSA: cross-sectional area
PCR: polymerase chain reaction
REDCap: Research Electronic Data Capture
SSS: slit skin smear
TPT: difference between the thickest and thinnest points along the nerve
UHB: University Hospital of Brasília
WHO: World Health Organization
